## Abstract

**Background:**

Humeral shaft fractures account for 1 to 3% of all fractures in adults and for 20% of all humeral fractures. Non-operative treatment is still the standard treatment of isolated humeral shaft fractures, although this method can present unsatisfactory results. Surgical treatment is reserved for specific conditions. Modern concepts of internal fixation of long bone shaft fractures advocate relative stabilisation techniques with no harm to fracture zone. Recently described, minimally invasive bridge plate osteosynthesis has been shown to be a secure technique with good results for treating humeral shaft fractures. There is no good quality evidence advocating which method is more effective. This randomised controlled trial will be performed to investigate the effectiveness of surgical treatment of humeral shaft fractures with bridge plating in comparison with conservative treatment with functional brace.

**Methods/Design:**

This randomised clinical trial aims to include 110 patients with humeral shaft fractures who will be allocated after randomisation to one of the two groups: bridge plate or functional brace. Surgical treatment will be performed according to technique described by Livani and Belangero using a narrow DCP plate. Non-operative management will consist of a functional brace for 6 weeks or until fracture consolidation. All patients will be included in the same rehabilitation program and will be followed up for 1 year after intervention. The primary outcome will be the DASH score after 6 months of intervention. As secondary outcomes, we will assess SF-36 questionnaire, treatment complications, Constant score, pain (Visual Analogue Scale) and radiographs.

**Discussion:**

According to current evidence shown in a recent systematic review, this study is one of the first randomised controlled trials designed to compare two methods to treat humeral shaft fractures (functional brace and bridge plate surgery).

**Trial registration:**

Current Controlled Trials: ISRCTN24835397

## Background

Humeral shaft fractures account for 1 to 3% of all fractures in adults [1,2] and for 20% of all humeral fractures [3]. These fractures have an annual incidence from 13 to 14.5 per 100,000 people [4,5]. Non-operative treatment is still the standard treatment for isolated humeral shaft fractures [6,7], although this method can present unsatisfactory results, such as, nonunion and shoulder impairment [8,9]. Fourteen percent of patients treated with this method have restricted range of motion and 12.6% have consolidation, with more than 10° of displacement [10].

Surgical treatment is recommended for patients with neurovascular injuries, medullar or brachial plexus injuries, and open fractures, for patients with multiple injuries, and for floating elbow and unsatisfactory reductions [11-13]. Humeral shaft fractures can also be treated surgically for the following indications: *Arbeitsgemeinschaft für Osteosynthesefragen* (AO)-Orthopaedic Trauma Association (OTA) type A fractures, proximal third oblique fractures and distal third shaft fractures [14-16]. Surgical options for treatment of humeral shaft fractures include open reduction and internal fixation with a compression plate, intramedullary nail osteosysthesis and minimally invasive bridge plate fixation. Open reduction and rigid internal fixation with absolute stability using dynamic compression plates [17-19] is today’s standard and is the more common surgical option for treatment of these fractures.

Modern concepts of internal fixation of shaft fractures of the long bones advocate relative stabilisation techniques with no harm to the fracture zone. These have largely been used for fractures of the leg and thigh for which they have become the gold standard treatment. In humeral shaft fractures, these concepts are also being applied with the use of the intramedullary nail [20-22]. In a systematic review, when compared to compression plate osteosynthesis, the use of the intramedullary nail presented a higher risk of shoulder impingement, shoulder pain, and restriction of movements [23]. Recently described by Livani and Belangero [24], minimally invasive bridge plate osteosynthesis with anterior access has been shown to be a secure technique with good results for the majority of humeral shaft fractures [25-27].

Good quality evidence, including trials comparing surgical and nonsurgical interventions for treating these fractures, is lacking [28]. This study will, therefore, be performed to investigate the effectiveness of surgical treatment of humeral shaft fractures with bridge plating in comparison with conservative treatment with a functional brace, considering patients’ superior limb function, their quality of life and treatment complications.

## Methods

This randomised controlled trial will follow the Consolidated Standards of Reporting Trials (CONSORT) Statement [29]; it will be performed in the Hand and Upper Limb Surgery Institute of the Orthopaedics and Traumatology Department of Universidade Federal de Sao Paulo and was approved by the ethical committee (CEP UNIFESP 1595/09). The project is registered in the Current Controlled Trials database (ISRCTN 24835397 http://www.controlled-trials.com/ISRCTN24835397), and was cited by a Cochrane Systematic Review [28]. This study has its funding approved under the process number 2011/21611-2 by a government-based noncommercial agency: Fundação de Amparo à Pesquisa do Estado de São Paulo (FAPESP).

### Inclusion criteria

All patients eighteen years of age or older, with completely deviated humeral shaft fractures (between 4 cm distal to the surgical neck of the humerus and 4 cm proximal to the superior border of the olecranon fossa), who agree to participate and give written informed consent, will be included in the study.

### Exclusion criteria

Patients with pathological or open fracture, previous disease in the limb that could influence the results, an immature skeleton, those whose fracture occurred more than 21 days previously or those with neurovascular-associated injury will be excluded. If patients do not wish to participate or are unable to understand or sign the informed consent form (due to conditions such as cognitive impairment, or mental illness), if poor compliance is expected, or if there any conditions that contraindicate any of the methods for randomized, will also be considered exclusion criteria. Patients who have high risk of anaesthesiology-associated problems will also be excluded.

### Sample size

The sample size was calculated for a significance level of 0.05, statistical power of 90% and SD of 15% in Disability of the Arm, Shoulder and Hand (DASH) scores and an absolute difference between the groups of 10 points in the DASH scores. It was calculated that 50 patients were needed in each group [30,31]. Allowing for a 10% loss to follow up at 24 weeks, we aim to recruit a total of 110 patients.

### Randomisation and allocation

The randomisation sequence will be generated by computer software (http://www.randomizer.org), creating a list from 1 to 110, each number being related to one of the two proposed methods of treatment. We will perform simple (unrestricted) randomisation, making the intervention assignment unpredictable, including the last 10 participants. According to this list, inside each of the 110 opaque sealed envelopes numbered from 1 to 110, will be a piece of paper containing the words ‘functional brace’ or ‘bridge plate.

Participant allocation will be performed after explaining the protocol and describing both of the procedures to be randomised, and after participants have agreed to take part and signed the informed consent form (Additional file 1 and Additional file 2). They will also be clinically evaluated to determine whether they are suitable candidates for surgery. After this, an independent person will open the envelope before proceeding to the intervention (Figure 1).

**Figure 1 F1:**
[figure not shown]
**Flow of participants.** Diagram shows the planned flow of participants through each stage of the study.

### Intervention methods

#### Nonsurgical treatment (functional brace)

Patients randomised to nonsurgical treatment will undergo closed reduction and initial immobilisation with a coaptation U-splint [32] (Figure 2) from the axilla to the elbow, ending in the deltoid. After 14 days, the immobilisation will be replaced by a functional brace [6] (Figure 3) allowing the patients to move their shoulder and elbow freely to exercises and rehabilitation. This brace will be kept until fracture consolidation, determined on radiography by two previously-assigned assessors. Any disagreements will be resolved by discussion with a third assessor.

**Figure 2 F2:**
[figure not shown]
Initial immobilisation with the splint.

**Figure 3 F3:**
[figure not shown]
Functional brace.

#### Surgical treatment (bridge plate osteosynthesis)

Patients randomised to surgical treatment will undergo preoperative evaluation of age, clinical condition (acute infection) and co-morbidities. The intervention will take place in the surgical centre of the institution, where four previously-specified surgeons, who are experienced with the surgical technique described by Livani and Belangero [24], will perform the surgical procedures. After the anaesthetic procedure, the patient will be kept in the horizontal dorsal decubitus position and two incisions will be made. The 3 to 5 cm proximal incision will access the proximal fragment between the biceps *brachii* muscle medially and the deltoid muscle laterally. The 3 to 5 cm distal incision will expose the anterior humeral cortex of the distal fragment, after dissection of the lateral cutaneous nerve of the forearm, and after the brachialis muscle is split longitudinally (Figure 4). In distal-third fractures, the lateral column of the distal humerus will be accessed with subperiosteal dissection of the lateral supracondylar crest and reflection of the *brachioradialis* and extensor *carpi radialis longus* muscles and the radial nerve. After indirect reduction under fluoroscopy, a narrow 4.5-mm dynamic compression plate (DCP) will be used and will be introduced in a proximal to distal direction (Figure 5). In fractures of the distal third of the humeral shaft, the plate will be introduced in a distal to proximal direction. Two to three screws will be inserted in each bone fragment. After osteosynthesis, final radiographs will be obtained, and the wound will be sutured and bandaged The patient will be kept immobilised with a sling until ambulatory evaluation.

**Figure 4 F4:**
[figure not shown]
Surgical incisions for minimally invasive bridge plate osteosynthesis.

**Figure 5 F5:**
[figure not shown]
Postoperative radiography.

### Treatment after the intervention

Patients from both of the randomised groups will be included in the same rehabilitation programme. Free-elbow passive and active motion and pendulum exercises for the shoulder will be allowed as soon as the patient can tolerate them. Internal and external shoulder rotations will be introduced 6 weeks after the intervention.

### Outcome assessment

All study participants will be evaluated at 2 and 4 weeks; 2, 6 and 12 months after the intervention. Radiographic evaluations, pain measurements using the visual analogue scale (VAS) [33], and application of the DASH [30,34] (Additional file 3 and Additional file 4), Short Form (SF)-36 and Constant shoulder score questionnaires will be performed by professional orthopaedists and physiotherapists who will not be directly associated with the study. Assessors will be blinded to the treatment assignment. Prior to outcome functional assessments, patients will be instructed not to reveal their treatment and will have their fractured arm covered with an opaque gown, identical in both groups [35].

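### Assessor blinding is claimed for every assessment, but radiographs cannot be read blind, and it does not protect the patient-reported outcomes

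*Protocol article*

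**What the plan says.** The Outcome assessment section gives one list of assessments, beginning "Radiographic evaluations, pain measurements using the visual analogue scale (VAS) [33], and application of the DASH" and continuing with SF-36 and Constant. These "will be performed by professional orthopaedists and physiotherapists who will not be directly associated with the study". The next sentence reads "Assessors will be blinded to the treatment assignment", with no outcome excepted.

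Two masking measures follow. The first is "Prior to outcome functional assessments, patients will be instructed not to reveal their treatment". The second is that patients "will have their fractured arm covered with an opaque gown, identical in both groups".

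Under Surgical treatment, "a narrow 4.5-mm dynamic compression plate (DCP) will be used", with screws in both fragments. The functional brace arm receives no implant.

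Under Secondary outcomes, the radiographic outcomes are consolidation (healed or not healed) and displacement and angulation of the fragments. That section does not say who reads the films. The only reader rule in the article is under Nonsurgical treatment: "This brace will be kept until fracture consolidation, determined on radiography by two previously-assigned assessors", with a third assessor for disagreements. The primary outcome is the DASH at 6 months.

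**The concern.** The blinding sentence covers radiographic evaluation, yet an implant present in one arm only identifies that arm on the film. The plan thus states a property that its radiographic outcomes do not have. This matters most for consolidation, a yes/no judgement: a reader who knows the allocation may settle doubtful films differently in the two arms.

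The same sentence also follows the DASH in the list. A reader may credit the primary outcome with protection from bias that blinding the form's administrator does not give, because the score consists of the patient's own answers.

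**Working it through.** **1. Radiographs**

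- Claim: radiographic evaluation is in the list, and the assessors are blinded without exception (Outcome assessment).
- Fact: plate and screws in the surgical arm, none in the brace arm (Surgical treatment).
- Masking: patient silence and a gown, both introduced for functional assessments (Outcome assessment). Neither acts on a film.
- Could the film be masked another way? A bridge plate fixed to both fragments spans the fracture. Covering the implant would tend to cover the site where healing and alignment are judged.
- Result: all three radiographic outcomes (consolidation, displacement, angulation) are read with the allocation visible.

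**2. Patient-reported outcomes**

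- Patients are told not to reveal their treatment, so they know it. The article nowhere says that patients are blinded.
- The VAS is marked by the patient (Secondary outcomes); DASH and SF-36 are questionnaires.
- Result: silence and a gown can keep the administrator unaware of the arm. They do nothing about the patient's own knowledge.

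**3. Who reads the films**

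- Nonsurgical treatment: two previously assigned assessors plus a third. The rule decides how long the brace is kept.
- Outcome assessment: clinicians outside the study evaluate radiographs in all participants.
- Secondary outcomes: consolidation is defined once for both arms, with no reader named.
- If the two groups of assessors are the same people, they know who is in the brace arm, because their reading decides when the brace comes off. If they are different people, it is not stated whether outcome films get double reading and adjudication. Either way the three sections need reconciling.

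**4. Illustration for the primary outcome**

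Inputs from Sample size: alpha 0.05 (two-sided assumed), power 90%, SD 15 (written as 15%, read as points), difference 10, 50 per group.

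The plan's figure first:

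n per group = 2 × (1.960 + 1.282)² × 15² / 10² = 2 × 10.51 × 2.25 = 47.3, so 48. The exact t-test needs 49. The stated 50 is reproduced, with power of about 91%. No figure in the plan is disputed here.

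Now suppose there is no true difference, but knowledge of treatment shifts self-reported DASH by b points in one arm. The documents give no value for b, so the values below are assumptions.

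SE = 15 × √(2/50) = 3.0

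Rejection probability = Φ(b/3 − 1.96) + Φ(−b/3 − 1.96)

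| Assumed shift b (DASH points) | Two-sided rejection rate |
|---|---|
| 0 | 5% |
| 2 | 10% |
| 3 | 17% |
| 5 | 38% |

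This shows how sensitive the test would be to such a shift. It does not show that a shift will occur.

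**The case against.** The strongest reply is that the protocol claims assessor blinding only and is open about patients knowing their arm. For the person handing over the forms, silence and an identical gown are coherent measures. Patient knowledge is inherent in comparing an operation with a brace. This stands. A reader might infer that the blinding statement is false for the DASH, but the text does not support that. What can be said is that assessor blinding does not protect the DASH.

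A second reply is that the two-assessor rule governs brace duration, so the surgical section needs no counterpart. This also stands. A reader might infer that consolidation is read under different rules in the two arms. No section says so: the outcome text covers all participants and defines consolidation once. A condensed article may also leave the detailed reading rule and healing criterion to the full protocol, so their absence is not itself a fault. What remains is that the article does not make clear how its two descriptions of film assessors relate.

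A third tempting inference is that only the Constant score, one instrument of five, can be blinded. The article calls it a questionnaire and does not say which parts an examiner measures, and such a count confuses who administers an instrument with who answers it. Nor does anything show that the gown fails to hide a splint or brace at the early visits.

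None of these replies reaches the radiographs. The objection that they are secondary outcomes is correct and limits the consequence, but the statement is still wrong for them.

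**Conclusion.** The concern holds in limited form. The unqualified blinding statement is wrong for the radiographic evaluations: consolidation, displacement and angulation cannot be read blind as planned. This rests only on the implant being visible on film and present in one arm. For DASH, VAS and SF-36 the statement can be true of the administrator, but it gives no protection against the patient's knowledge of treatment, and the primary result has to be interpreted with that in mind.

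The size of either bias cannot be derived from the documents. The 10% to 38% range for the DASH depends wholly on assumed shifts of 2 to 5 points, and the article gives no figure for reader agreement on consolidation. Nothing here alters the sample size or the primary analysis.

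**What to change.** - In Outcome assessment, limit the blinding sentence to functional examiners and to the administration of questionnaires.
- State that patients and radiograph readers are not blinded, and interpret the patient-reported and radiographic outcomes accordingly, acknowledging possible reporting bias in the DASH.
- Reconcile Nonsurgical treatment, Outcome assessment and Secondary outcomes so that, for outcome purposes, the already assigned assessors read the films of both arms by the same rule (two readers, a third for disagreements) at the same scheduled visits. This concerns outcome reading only and leaves the decision on brace duration as it is.

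The cost is a change of protocol wording and slightly more film reading. The downside is that the trial's stated blinding becomes less favourable.

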### Primary outcome

Our primary outcome will be the DASH [30,34] scores 6 months after the procedure (either surgical or nonsurgical) for treatment of humeral shaft fractures. The final score will be calculated using the specified formula:

$$\text{DASH}\;\text{score}=\left(\text{Raw}\;\text{score}-30\right)/1.2.$$

The two optional modules of the DASH questionnaire will not be applied in this study.

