### Data analysis

Patients, who for any reason demonstrate that their treatment may require additional interventions, will be followed up, and their results will be included in the group into which these patients had initially been randomised, according to the intention-to-treat principle. The Pearson chi-squared test will be used to analyse the results from the two groups in relation to the categorical variables, and Student’s *t*-test will be used to compare the groups in relation to the numerical variables. Student’s *t*-test (parametric) will be used to compare the clinical evolution of each group 2, 4, 8, 24 and 48 weeks after the intervention. For the primary outcome, a significance level of 5% (alpha = 0.05) will be used for all statistical tests, such that tests presenting a *P*-value less than 0.05 will be considered statistically significant. For the secondary outcomes we will consider an alpha value of 0.02.

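### Outcome visits are counted from an undated, arm-specific procedure instead of randomisation, and the same visits are given as 6 and 12 months in some sections and 24 and 48 weeks in others

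*Protocol article*

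**What the plan says.** **Time origin.** Under Primary outcome, the endpoint is DASH "scores 6 months after the procedure (either surgical or nonsurgical) for treatment of humeral shaft fractures". The abstract (Methods/Design) puts it as "The primary outcome will be the DASH score after 6 months of intervention". Under Outcome assessment: "All study participants will be evaluated at 2 and 4 weeks; 2, 6 and 12 months after the intervention". No section counts outcome visits from randomisation.

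**What comes before the origin in each arm.** Randomisation and allocation has the envelope opened after consent and a clinical check of fitness for surgery, and before the intervention. It sets no maximum interval. The surgical section describes a preoperative evaluation and then the operation, with no dates. The nonsurgical section begins with closed reduction and a U-splint, and continues: "After 14 days, the immobilisation will be replaced by a functional brace".

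**Timing of the visits.** The primary visit is at 6 months in the abstract, in Outcome assessment and in Primary outcome. Under Data analysis, the t-test "will be used to compare the clinical evolution of each group 2, 4, 8, 24 and 48 weeks after the intervention". Under Sample size: "Allowing for a 10% loss to follow up at 24 weeks, we aim to recruit a total of 110 patients".

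**The concern.** DASH is expected to fall as the fracture heals, so a patient seen later after injury tends to score better for that reason alone. Randomisation balances the time from injury to allocation between the arms, on average. It does not balance the time from allocation to a procedure whose nature depends on the arm. If that interval differs systematically, a visit at a fixed time after the procedure falls at different times since randomisation and injury in the two arms, and part of the DASH difference reflects timing.

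The origin also fits poorly with the intention-to-treat principle stated under Data analysis. A patient who never receives the allocated procedure has no day 0 under the rule as written.

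The month and week figures raise a different problem. Staff who schedule from Outcome assessment and an analyst who works from Data analysis would place the primary visit about two weeks apart.

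**Working it through.** **1. The plan's own sample size, to see whether timing enters it.** Inputs from Sample size: difference 10, SD 15, alpha 0.05 (taken as two-sided), power 90%.

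n per group = 2 × [15 × (1.960 + 1.282) / 10]² = 47.3, so 48. Solving for the t-test gives 48.3, so 49. The stated 50 is reproduced within 2 patients. For loss to follow-up, 100 × 1.10 = 110 as stated; 100 / 0.90 gives 112 when rounded up to an even total. No time origin enters these formulas, so the sample size is unaffected.

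**2. Months against weeks** (365.25 days per year).

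| Visit | Calendar length | Weeks stated | Gap |
|---|---|---|---|
| 2 months | 365.25 / 6 / 7 = 8.7 weeks | 8 | 0.7 weeks |
| 6 months | 365.25 / 2 / 7 = 26.1 weeks | 24 | 2.1 weeks |
| 12 months | 365.25 / 7 = 52.2 weeks | 48 | 4.2 weeks |

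The gaps are the same in both arms, so they cannot create a difference between arms.

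**3. Candidate dates for day 0.**

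- Plate arm: the operation. The interval from envelope opening is not given.
- Brace arm, more natural reading: the closed reduction with U-splint, as the first nonsurgical procedure. The interval from envelope opening is not given.
- Brace arm, less natural reading: the fitting of the brace, 14 days later.

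The direction of an offset depends on which of these applies. A wait for surgery would place plate patients later after injury at the 6-month visit. Counting from the brace fitting would place brace patients later. If both applied, they would partly cancel.

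**4. Size of a possible bias.** The protocol gives neither a DASH slope near 6 months nor an offset, so both are assumed: slope 0.1 to 1.0 points per week, offset 1 to 3 weeks. Bias b = slope × offset. The standard error of the difference with 50 per group is 15 × √(2/50) = 3.0.

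Chance of a significant result when the arms do not differ at equal time since injury: 1 − Φ(1.96 − b/3) + Φ(−1.96 − b/3).

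Power when the bias opposes a true 10-point effect: Φ((10 − b)/3 − 1.96). With b = 0 this is 0.915.

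| Slope (points/week) | Offset (weeks) | b (points) | Type I error | Power |
|---|---|---|---|---|
| 0.1 | 1 | 0.1 | 0.050 | 0.91 |
| 0.1 | 2 | 0.2 | 0.051 | 0.90 |
| 0.25 | 2 | 0.5 | 0.053 | 0.89 |
| 0.5 | 2 | 1.0 | 0.063 | 0.85 |
| 1.0 | 2 | 2.0 | 0.102 | 0.76 |
| 1.0 | 3 | 3.0 | 0.170 | 0.65 |

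The assumed range thus runs from almost no effect to a material one, and nothing in the protocol places the trial within it.

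**The case against.** The strongest reply is that no differential timing is shown. The protocol gives no waiting time for surgery or for reduction. Fitness for surgery is checked before allocation, and the envelope is opened before the intervention in both arms. This stands: a lag is possible, not documented.

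Second, the brace-arm origin is clearer than it may look. The splint is described as initial immobilisation, and the first visit, at 2 weeks, coincides with the change to the brace, which fits a clock that starts at reduction. This stands too. The 14-day ambiguity rests on the less natural reading, although the text does not exclude it: the allocation slip names the functional brace, and so does the abstract's account of nonoperative care.

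Third, the two visit lists match one to one if a month is taken as four weeks, so they are probably the same five visits loosely converted. That is the likely explanation, but the lists still give different times for the primary and final visits.

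Fourth, later surgery is largely dealt with: Data analysis keeps patients who need additional interventions in their randomised group, and nothing suggests that their clock restarts.

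Fifth, counting follow-up from treatment is a legitimate design choice, because time since operation has clinical meaning. It is, but the choice gives up a common origin that exists in both arms, and the protocol gives no reason for doing so.

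The exclusion of "those whose fracture occurred more than 21 days previously" does not help either side. It applies equally to both arms at entry and sets no limit on the interval between allocation and the procedure.

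**Conclusion.** The point holds as a weakness in the timing rule and a contradiction in the stated time points. The rule counts the primary visit from an undated event after randomisation that differs by arm, so it can produce arm-dependent assessment times. Under the assumed slopes and offsets the bias is 0.1 to 3.0 DASH points, or 1% to 30% of the 10-point target. Its true size and direction are unknown.

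A reader might infer that the arms are in fact compared at different times since injury, or that a bias of several points is to be expected. The protocol supports neither, since the offset and the slope are both assumptions. Nor does the discrepancy between months and weeks (about 2 weeks at the primary visit, 4 at the last) add to any between-arm bias, because both arms share it.

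Severity is minor to moderate. The reason to act is that a better rule is available at little cost.

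**What to change.** Count all outcome visits from the date of randomisation (the opening of the envelope) in both arms, whatever treatment is received and whenever it starts. This also gives a visit date to a patient who never has the allocated procedure.

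State the primary and final time points once, in one unit, and use them in the abstract (Methods/Design), Sample size, Outcome assessment, Primary outcome and Data analysis. If calendar months are what is meant, 26 and 52 weeks would express them. Make sure that the dates of injury, randomisation and first treatment are recorded, so that any offset can be described.

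The change concerns outcome visits only; it leaves treatment and rehabilitation schedules as they are. It costs a wording amendment and a scheduling rule. Plate patients may be seen slightly earlier after their operation than under the present rule. As recruitment has begun, visits already held can be reported by their actual time since randomisation.
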